### 3.4 Outcomes

#### 3.4.1 Primary outcome

The primary outcome of the study is the number of deviations from the PALS guidelines made by the teams during the management of a standardized simulated scenario of non-shockable PCA.

Deviations from PALS guideline recommendations are defined as delays and errors according to a novel checklist we derived from the previously published checklist by Wolfe et al[20], denominated c-DEV, by integrating it with evidence-based guidelines,[6-8,11] previously reported scoring tools,[40-43] and checklists.[37,44,45] We named our new modified checklist c-DEV15plus. It includes 15 items, which represent correct critical actions for paediatric resuscitation (Table 1).

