After the scenario, all participants complete a demographic survey reporting their sex, age, year and type of residency program, experience in simulation and resuscitation, and time from PALS/P-BLS/BLS/ALS/ACLS certification. In addition, all the team leaders complete the NASA-TLX and the team leaders in the intervention arm also evaluate the app usability, by completing the SUS. Subsequently, all participants participate in a 15-minute debriefing during which they receive feedback about their performance, and the teams in the intervention arm are able to provide feedback about the app. During this phase, the debriefer reports the feedback received on the app in a specific CRF.

The videos of the scenarios will be evaluated by two independent, and previously trained, reviewers expert in paediatric emergency medicine and simulation. Training of the reviewers, on

RCT-unrelated PCA simulation videos, will be conducted by the principal investigator (FC), until the reviewers will reach at least 80% inter-rater agreement with the principal investigator. No more than two weeks will lapse between the training and the assessment of the RCT videos. The reviewers will use a standardized data collection form where actions performed by the team and time to performance will be assessed and recorded. Disagreements between reviewers will be resolved by consensus with a third independent reviewer, expert in paediatric emergency medicine and simulation. Inter-rater reliability between reviewers will be monitored and reported. Data pertaining the CPR quality from the manikin software will be extracted and recorded on a specific CRF. The scores on the c-DEV15plus, and all the secondary outcomes will be calculated by outcome assessors based on the data coded and reported by the video reviewers on the CRFs.

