### **3.8.2 Data analysis plan**

The results will be summarized for each study group with counts and percentages for categorical variables, mean and standard deviation (SD) or median and interquartile range for quantitative variables, as appropriate. The normality of the quantitative variables will be checked with the Shaphiro-Wilk test.

The c-DEV15plus scale, the performance and time to accomplish specific resuscitation interventions, NASA-TLX, CPT and cardiopulmonary resuscitation metrics will be compared between groups with one-way ANOVA model, followed by the Tukey-Kramer multiple comparisons adjustment procedure in case of statistical significance.

The outcomes will also be analysed with a linear mixed model considering the team as a cluster to evaluate the influence of participants' characteristics on the outcome. To take into account the correlation of the observations within a team, we will specify an undetermined correlation matrix. In case of a not normal distribution of the model residuals, we will proceed with a transformation in order to normalize the distribution.

Both intention-to-treat and per-protocol analyses will be performed.

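### The deciding c-DEV15plus comparison has arm as its only term, although two leader covariates fixed before allocation are already collected; adjusting for them is a low-cost precision gain of unknown size, not the repair of an error

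*Protocol*

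**What the plan says.** The outcome is measured once per team. Section 3.4.1: "The primary outcome of the study is the number of deviations from the PALS guidelines made by the teams". Section 3.8.2 states that this score "will be compared between groups with one-way ANOVA model". The pairwise step is conditional on that test: "followed by the Tukey-Kramer multiple comparisons adjustment procedure in case of statistical significance". The abstract names the same one-way model, and section 3.8.1 bases the sample size on a single-factor ANOVA. The primary model is therefore stated, not left open.

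Section 3.6 has every participant complete a survey after the scenario. Its fields include "year and type of residency program, experience in simulation and resuscitation, and time from PALS/P-BLS/BLS/ALS/ACLS certification". Section 3.2 requires every team leader to be PALS-certified, so time since PALS certification is defined for every leader. Section 3.3 stratifies by site and residency specialty only.

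Participant characteristics enter the analysis in one place. Section 3.8.2, in a sentence cut here before its last words: "The outcomes will also be analysed with a linear mixed model considering the team as a cluster to evaluate the influence of participants' characteristics on". That model is additional to the ANOVA, names no covariate, and does not supply the deciding arm contrast.

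**The concern.** A one-way ANOVA leaves in the error term whatever between-team variation the leader's training year and time since certification would explain. There are reasons to expect some. The score counts departures from PALS guidance, the leader is the one member who must hold PALS certification (3.2, 3.3), and the app is built to guide the leader (3.5.1). Stratification does not balance either variable, so with 35 teams per arm a chance imbalance in leader experience is possible, and the deciding analysis would not account for it.

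In a linear model, adjusting for values fixed before allocation leaves the target unchanged: the mean difference in points between arms. What is at stake is the width of the three pairwise intervals and the power for differences smaller than the planned 3.00 points. The validity of the comparison is not at stake.

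**Working it through.** **Inputs from the protocol (3.8.1).** Difference 3.00 points; within-group SD 2.20; 5% level; 80% power; Tukey-Kramer over three arms; 29 teams per arm, raised by 20% to 35 (29 × 1.2 = 34.8).

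**Assumption.** R² is the share of within-arm c-DEV15plus variance explained jointly by the two leader covariates. The protocol gives no value. The range used is 0% to 30%.

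**Formulas.**
- Standard error of a pairwise difference: SE = SD × √(2/n).
- Adjusted SE = SE × √(1 − R²).
- Critical value = q(0.95; 3, df)/√2, where q is the studentized range quantile and df = 3(n − 1), less 2 when two linear covariates are fitted.
- Power from the noncentral t with noncentrality difference/SE.

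**Step 1: the plan's own figure.** At 12 per arm the pairwise Tukey power for 3.00 points is 80.7%, so 29 per arm does not follow from the stated inputs. At 29 per arm, SE = 2.20 × √(2/29) = 0.578, the critical value is 2.386, and power for 3.00 points is 99.7%. At 35 per arm, SE = 2.20 × √(2/35) = 0.526 and power is 99.95%. The mismatch over 29 is a separate matter. It is relevant here only because it shows that, on the stated inputs, the unadjusted test has ample power for its target.

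**Step 2: effect of adjustment at 35 per arm.** The first row is the planned ANOVA; the other rows lose two degrees of freedom.

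| R² (assumed) | Residual SD | SE | Reduction in SE | Difference detectable with 80% power | Power for 2.0 points | Power for 1.5 points |
|---|---|---|---|---|---|---|
| Unadjusted | 2.20 | 0.526 | – | 1.70 | 92.1% | 68.2% |
| 0% | 2.20 | 0.526 | 0% | 1.70 | 92.1% | 68.2% |
| 5% | 2.14 | 0.513 | 2.5% | 1.65 | 93.4% | 70.7% |
| 10% | 2.09 | 0.499 | 5% | 1.61 | 94.7% | 73.4% |
| 20% | 1.97 | 0.470 | 11% | 1.52 | 96.8% | 78.9% |
| 30% | 1.84 | 0.440 | 16% | 1.42 | 98.4% | 84.7% |

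Check of the last row: √(1 − 0.30) = 0.837, and 0.526 × 0.837 = 0.440. The 2.0 and 1.5 points are illustrations; the protocol's only target is 3.00.

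**Step 3: interval width.** The simultaneous 95% half-width at 35 per arm is critical value × SE = 2.378 × 0.526 = 1.25 points unadjusted. It falls to 1.19 at R² = 10% and 1.05 at R² = 30%.

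**Step 4: cost if the covariates explain nothing.** Losing two degrees of freedom moves the detectable difference at 35 per arm from 1.696 to 1.697 points.

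**The case against.** The strongest reply is that nothing here is stated wrongly. An unadjusted comparison of randomised teams is valid, and it matches the model used for the sample size. On the stated inputs it has more than 99% power at the trial's own target. That all stands, and it limits this point to a precision improvement.

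Second, the size of the gain rests wholly on an assumed R², and it may be close to zero. The score comes from a team of three. Items such as placing the board or switching compressors need not follow the leader's training year. All leaders are PALS-certified, which may narrow their range of experience. This also stands, and is why the range starts at 0%.

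Third, the planned mixed model already looks at participant characteristics. That is partial cover: it is supplementary, its covariates are unnamed, and it does not provide the contrast on which the primary conclusion rests.

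Fourth, the post-scenario survey is the only place where the protocol says these variables are recorded, and it lists several certificates together. Nothing says that a certification date is captured at the eligibility check. The fix must therefore work with the survey fields. Year of residency and time since a certificate are facts settled before allocation, so recording them afterwards does not rule them out. Self-rated experience could be coloured by how the scenario went.

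A reader might infer that the primary result would be biased, or the trial underpowered, without adjustment. The protocol supports neither. Randomisation protects the unadjusted contrast from bias, and the power figures above rule out a shortfall at 3.00 points with SD 2.20. Nor does the protocol show that the two variables do explain team-to-team variation; that is plausible but undocumented.

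**Conclusion.** The point holds as a recommendation on efficiency. The deciding model omits two covariates that are collected anyway, fixed before allocation and left unbalanced by the stratification. Including them keeps the same estimand and costs almost nothing.

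The gain is of unknown size. With an assumed R² of 0% to 30%, the SE falls by 0% to 16%, and the 80%-power detectable difference at 35 per arm goes from 1.70 points to between 1.70 and 1.42. These figures also assume SD 2.20, linear covariate terms and 35 analysable teams per arm. The benefit would show in narrower intervals, and in power if either app-versus-control difference is well below 3 points. It would not alter the planned test at 3.00 points, which already has about 99.7% power at 29 per arm.

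**What to change.** In section 3.8.2, prespecify before unblinding that the primary analysis of c-DEV15plus is a team-level linear model with arm, the leader's year of residency and the leader's time since PALS certification, the last two as linear terms. Apply Tukey-Kramer to the adjusted arm contrasts, and keep the unadjusted one-way ANOVA as a sensitivity analysis.

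Take both covariates from the factual survey fields already collected, using the PALS-specific value for time since certification. Check them against certification records where these are available. Do not adjust for self-rated experience.

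The cost is a change of wording, two degrees of freedom, and a completeness check of two fields for 105 leaders. Entering year as a category would use more degrees of freedom. If the covariates turn out not to be prognostic, there is no gain and a negligible loss.

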## 1. ABSTRACT

**Introduction:** Paediatric cardiac arrest (PCA), despite its low incidence, has a high mortality. Its management is complex and deviations from guideline recommendations occur frequently. We developed a new interactive tablet app, named PediAppRREST, to support the management of PCA. The app received a good usability evaluation in a previous pilot trial. The aim of the study is to evaluate the effectiveness of the PediAppRREST app in reducing deviations from guideline recommendations in PCA management.

**Methods and analysis:** This is a multicentre, simulation-based, randomized controlled, three-parallel-arm study. Participants are residents in Paediatric, Emergency Medicine, and Anaesthesiology programs in Italy. All 105 teams (315 participants) manage the same scenario of in-hospital PCA. Teams are randomized by the study statistician into one of three study arms for the management of the PCA scenario: 1) an intervention group using the PediAppRREST app; or 2) a control group (CtrlPALS+) using the Paediatric Advanced Life Support (PALS) pocket reference card; or 3) a control group (CtrlPALS-) not allowed to use any PALS-related cognitive aid. The primary outcome of the study is the number of deviations (delays and errors) in PCA management from PALS guideline recommendations, according to a novel checklist, named c-DEV15plus. The c-DEV15plus scores will be compared between groups with a one-way ANOVA model, followed by the Tukey-Kramer multiple comparisons adjustment procedure in case of statistical significance.

**Ethics and dissemination:** The Ethics Committee of the University Hospital of Padova, coordinating centre of the trial, deemed the project to be a negligible risk study and approved it through an expedited review process. The results of the study will be disseminated in peer-reviewed journals, and at national and international scientific conferences. Based on the study results, the PediAppRREST app will be further refined and will be available for download by institutions/health care professionals.

**Trial registration number:** NCT04619498

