### **2.1 Objectives**

The primary objective of this study is to determine, in a multicentre, randomized controlled trial, whether the use of the PediAppRREST app is associated with a reduction of deviations from international guidelines, in the management of a simulated PCA scenario, compared with the use of the PALS pocket reference card or with the use of no cognitive aid.

The secondary objectives are to further evaluate the usability of the PediAppRREST app and its impact on team members' workload, CPR quality, time to performance of critical resuscitation interventions, and overall team performance.

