### **3.8 Statistical Analysis**

#### ***3.8.1 Sample size calculation***

We calculated sample size on the basis of the results obtained during the previous observational simulation-based study and the pilot study that tested the app usability.[37,38] Based on the preliminary results from these studies, using a single factor ANOVA model, 29 scenarios per each of the three groups (PediAppRREST, CtrlPALS+, CtrlPALS-) are necessary to detect a difference of at least 3.00 points on the c-DEV15plus scale using the Tukey-Kramer

(Pairwise) multiple comparison procedure at a 5% significance level and 80% power. The common standard deviation within a group is assumed to be 2.20.

In consideration that some possible technical problems with video-recording or other study procedures could occur, we aim to increase the recruitment of participating teams by 20% per arm, to compensate for loss of statistical power due to a potential insufficient sample size. Hence, we plan to have 35 scenarios per arm, for a total of 105 scenarios, which will include overall 315 residents divided in teams of three.

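### Tukey-Kramer comparisons run only if the ANOVA F-test is significant: an unneeded gate that leaves the two app contrasts unplanned if F misses (minor)

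*Protocol*

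**What the plan says.** - **Analysis rule.** Protocol 3.8.2 compares the c-DEV15plus scale, the intervention times, NASA-TLX, CPT and the CPR metrics between arms by one-way ANOVA, "followed by the Tukey-Kramer multiple comparisons adjustment procedure in case of statistical significance". The Abstract gives the same rule for c-DEV15plus.
- **Objective.** Section 2.1 asks whether the app reduces deviations "compared with the use of the PALS pocket reference card or with the use of no cognitive aid". That is two contrasts: app versus card and app versus no aid.
- **Sample size.** Section 3.8.1 works within a single-factor ANOVA model. It asks for 29 teams per arm, given a 3.00-point difference and an assumed SD of 2.20. The test behind that number is Tukey-Kramer applied to pairs of arms, described as a "multiple comparison procedure at a 5% significance level and 80% power". No preliminary F-test is mentioned. The 20% allowance gives 35 teams per arm.
- **Other output.** Section 3.8.2 also promises summaries for each arm, with no condition attached. It adds a linear mixed model, whose stated purpose is to examine the influence of participants' characteristics.

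**The concern.** The F-test asks whether the three arm means are all equal. The trial asks two narrower questions about the app, and Tukey-Kramer answers them with its own 5% familywise control. A significant F is not needed to make the pairwise tests valid.

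The gate has three consequences:

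- The combined procedure is slightly conservative.
- It can block an app contrast that Tukey-Kramer alone would declare.
- If F misses, the protocol plans no adjusted estimate or interval for either contrast in the objective. After a non-significant result, that interval is what a reader needs in order to see which app effects remain plausible.

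The same rule covers the listed secondary outcomes, for which 3.8.1 gives no planning effect.

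**Working it through.** **Inputs.** From 3.8.1: SD 2.20, difference 3.00, 5% level, 29 per arm before and 35 after the allowance. Assumption: the protocol gives no arm means, so the card arm's position is unknown. It is set midway below unless stated, and was varied over the whole range in step 5.

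**1. The plan's own figure.** Per-pair Tukey power comes from a noncentral t with critical value q(0.95; 3, 3(n−1))/√2 and noncentrality 3.00/(2.20·√(2/n)).
- n = 12: 80.7%.
- n = 29: 99.7%.

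The stated 29 is therefore not reproduced by this route. The allowance is: 29 × 1.2 = 34.8, so 35. The origin of 29 is a separate question and nothing below depends on it; results are given at both 29 and 35.

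**2. Where the gate bites (35 per arm, 102 df).**
- Tukey: q = 3.364, so |t| ≥ 3.364/√2 = 2.378.
- F critical value: F(0.95; 2, 102) = 3.085.
- Third observed mean exactly midway: the between-arm mean square is n·2(d/2)²/2 = nd²/4 and t² = nd²/(2s²), so F = t²/2. Significance needs |t| ≥ √(2 × 3.085) = 2.484.
- Third observed mean equal to one of the other two: F = 2t²/3. Significance needs |t| ≥ √(1.5 × 3.085) = 2.151, which is below the Tukey limit, so the gate does not bind.

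The gate blocks an outer contrast only when the third observed mean lies near the middle. At s = 2.20 with that mean exactly midway, the blocked band is an observed difference of 1.25 to 1.31 points at 35 per arm, and 1.38 to 1.44 at 29.

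**3. Familywise error, all means equal (simulation).** Tukey alone 5.0%; Tukey after a significant F 4.5%. Both hold at 29 and at 35 per arm.

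**4. Power for app versus no aid, card midway (simulation).**

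| True difference | n per arm | Tukey alone | Tukey after F | Loss (points) |
|---|---|---|---|---|
| 3.00 | 29 | 99.72% | 99.68% | 0.04 |
| 3.00 | 35 | 99.95% | 99.94% | 0.01 |
| 1.50 | 35 | 68.2% | 66.8% | 1.4 |

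In the 3.00-point rows app versus card differs by 1.5 points, and its power is unchanged by the gate: about 58.5% at 29 and 68.2% at 35.

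**5. Worst case.** True ranges from 0.2 to 3.0 points were searched, with the card at 0, 25, 50, 75 and 100% of the range, at 29 and 35 per arm. The largest losses were about 1.5 points for app versus no aid, 1.6 for at least one app contrast and 1.7 for any pair. The largest losses for an app contrast came at ranges of about 1.2 to 1.4 points with the card midway.

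**6. How often the contrasts would go unplanned.** F has noncentrality nd²/(2·SD²) with the card midway.
- d = 3.00, n = 29: 29 × 9/9.68 = 26.96; F misses in about 0.3% of trials.
- d = 3.00, n = 35: 35 × 9/9.68 = 32.54; about 0.05%.
- d = 1.50, n = 35: 35 × 2.25/9.68 = 8.14; about 29%.

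In most of that 29% Tukey would not be significant either: only 1.4 points are lost rejections for app versus no aid. The rest is missing interval estimates.

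**The case against.** ANOVA followed by a post-hoc test is a conventional and valid sequence. The gate can only make the procedure more conservative, so it cannot create a false claim. At the effect the trial is sized for, F is significant in over 99.7% of trials and the contrasts would nearly always be run. If F missed, the unconditional arm summaries would still let a reader form unadjusted differences. An analysis plan that is not shown could also promise intervals. Most of this stands, and it is why the point is minor. It does not remove the point: the condition is written into the protocol twice, buys no error control, and governs adjusted estimates that neither the summaries nor the mixed model, as described, would supply.

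A reader might infer three stronger claims that the documents do not support:

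- **The gate seriously weakens the trial.** Steps 4 and 5 show a loss near zero at the planning effect and small everywhere else. The missing gate in 3.8.1 is a mismatch of description and does not undermine the sample size.
- **The trial will suppress its main results.** This happens only if F misses, which is rare at 3.00 points.
- **Tukey-Kramer is the wrong method, and Dunnett's procedure with the app as reference is required.** Dunnett would fit the two-contrast objective, but it takes card versus no aid out of the primary error control. The protocol names all-pairs Tukey-Kramer in both the sample size and the analysis, and 3.5.2 says that the card has no published evidence of effectiveness, so the third comparison has a use. This is an optional trade-off and not the correction of an error.

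**Conclusion.** The point holds as a minor one. The gate is unnecessary, lowers the familywise error from 5.0% to about 4.5%, does not appear in the sample size basis, and leaves both contrasts of the primary objective without a planned adjusted estimate when F is not significant. The power cost is secondary: 0.01 to 0.04 percentage points for app versus no aid at the planning effect, 1.4 at a true 1.5-point difference with 35 per arm, and about 1.7 at most for any pair. The figures assume normal scores, a common SD of 2.20 and equal arms. The card arm's position is an assumption; it changes the size of the loss, but the loss stayed small at every position examined.

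**What to change.** Remove the closing condition from the Tukey-Kramer sentence in both the Abstract and 3.8.2. State that app versus card, app versus no aid, and card versus no aid are reported with Tukey-Kramer adjusted p-values and simultaneous 95% confidence intervals whatever the F result. The F-test may stay as a descriptive overall test.

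The cost is wording only: no extra teams, no new data, and the familywise error over the three pairs stays at 5%. The analysis would then match the procedure named in 3.8.1.

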### **3.3 Randomization, allocation concealment, and blinding**

Participants are randomized by the study statistician in teams of three, stratified by study site and residency program specialty. Randomization is conducted assuring that in every team there will be at least one PALS-certified team member assigned to the role of team leader. The same statistician assigns a unique team identification number to each team and prepares the list of participants associated with each team to be sent to the principal investigators. Participants are randomly divided in teams of three members per each scenario; the team leader is selected among PALS-certified residents whereas the other two members have to be at least BLS-certified. The teams are randomized with a 1:1:1 ratio in the intervention arm (PediAppRREST arm) and the two control arms.

The statistician also creates opaque sealed envelopes externally marked with the team identification number and containing a paper slip, which indicates the arm allocation for that specific team. Team group allocation is concealed until the simulation sessions. Randomization of participants to teams, and teams to the arms, is performed with SAS 9.4 (SAS Institute Inc., Cary, NC, USA) for Windows.

Due to the nature of the cognitive support tools used in the trial, blinding of participants as well as of research staff involved in the simulation sessions and video reviewers, is not possible. However, blinding of the statistician performing data analysis will be ensured. Data analysis is expected to be finalized by February 2022.

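### Minor efficiency gain: the primary objective holds two app contrasts, but Tukey-Kramer covers all three pairs, so the two deciding intervals are about 6% wider than 5% familywise control requires

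*Protocol*

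**What the plan says.** Protocol 2.1 states the primary objective as a reduction in deviations with the app "compared with the use of the PALS pocket reference card or with the use of no cognitive aid". Neither the primary nor the secondary objectives mention card against no aid.

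Protocol 3.8.2 compares the c-DEV15plus score between the three groups by one-way ANOVA, "followed by the Tukey-Kramer multiple comparisons adjustment procedure" if the ANOVA is significant. The abstract says the same. With three arms, Tukey-Kramer covers three pairwise differences.

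Protocol 3.8.1 bases the sample size on the same procedure: "29 scenarios per each of the three groups" are "necessary to detect a difference of at least 3.00 points on the c-DEV15plus scale using the Tukey-Kramer" pairwise method at 5% significance and 80% power. It adds: "The common standard deviation within a group is assumed to be 2.20". The number is then raised by 20% to 35 per arm, 105 teams in all. Section 3.3 fixes the allocation: "The teams are randomized with a 1:1:1 ratio".

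**The concern.** The primary question is many-to-one: one app arm against each of two control arms. An all-pairs adjustment also protects a third difference, card minus no aid, that answers no stated objective. That protection is paid for by a larger critical value on the two differences that do decide the trial. A procedure for exactly those two contrasts, such as Dunnett with the app as reference, holds the same 5% familywise error with a smaller critical value.

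At stake is precision: the width of the two primary confidence intervals, and power if the true effect is well below the planned one. This does not depend on whether the F-test acts as a gate; at the values examined below the gate costs practically nothing.

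**Working it through.** **Inputs.** Three arms at 1:1:1 (3.3). SD 2.20, target difference 3.00 points, 5% significance, 80% power, 29 per arm raised to 35 (3.8.1). Sidedness is not stated; two-sided is assumed, as Tukey-Kramer implies. Degrees of freedom are 3(n − 1): 84 at n = 29 and 102 at n = 35.

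**Step 1: the plan's own figure.** The Protocol does not say how power is defined for the pairwise procedure. The figure of 29 is reproduced by a simultaneous-interval definition: the probability that all Tukey intervals cover the true differences and that their full width, 2·q·s/√n, is below 3.00. Here q is the 95% point of the studentized range for three means and s the pooled SD. This gives 0.774 at n = 28 and 0.833 at n = 29, so 29 is the smallest n reaching 80%. The definition is inferred. Ordinary per-pair Tukey power from the noncentral t would need only 12 per arm. The inflation also reproduces: 29 × 1.2 = 34.8, rounded to 35.

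**Step 2: critical values.** Tukey-Kramer uses q(0.95; 3, df)/√2. Dunnett uses the two-sided 95% point for two contrasts with correlation 0.5 (equal arms), by numerical integration.
- n = 29: 2.386 (Tukey-Kramer), 2.250 (Dunnett).
- n = 35: 2.378 (Tukey-Kramer), 2.243 (Dunnett).

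**Step 3: interval width at 35 per arm.** The standard error of a difference is 2.20 × √(2/35) = 0.526. Half-widths are 2.378 × 0.526 = 1.25 and 2.243 × 0.526 = 1.18 points. The ratio 2.378/2.243 = 1.060, so Tukey-Kramer intervals are about 6% wider (Dunnett's are 5.7% narrower). Squared, 1.060² ≈ 1.124: in interval width, Dunnett on 105 teams is worth about 105 × 1.124 ≈ 118 teams under Tukey-Kramer.

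**Step 4: power per contrast at 35 per arm.** Noncentral t with noncentrality δ/0.526:

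| True difference δ (points) | Tukey-Kramer | Dunnett |
|---|---|---|
| 3.00 (planned) | 99.95% | 99.97% |
| 2.00 | 92.1% | 93.9% |
| 1.50 | 68.2% | 72.8% |
| 1.25 | 50.2% | 55.5% |
| 1.00 | 32.1% | 37.0% |

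The difference detectable with 80% power is 1.70 points against 1.62. At 29 per arm it is 1.87 against 1.79, and power at 3.00 points is 99.7% against 99.8%.

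**Step 5: effect on the stated sample size.** Under the inferred definition of step 1, Dunnett for the two app contrasts gives 0.761 at n = 25 and 0.827 at n = 26, so 26 per arm would meet the same criterion. The Tukey-based 29 is therefore conservative for a Dunnett analysis.

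**The case against.** The strongest reply is that nothing here is wrong. Tukey-Kramer controls familywise error for the two app contrasts, and the abstract, 3.8.1 and 3.8.2 all name it, so analysis and sample size agree and the penalty is already built into n. At the planned 3.00 points the loss is about 0.02 percentage points. The differences where it reaches about 5 points, 1 to 1.5, are illustrative; the Protocol does not name them as relevant. All of this stands, and it makes the point minor.

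It may also be said that the sponsor could want card versus no aid under familywise control. The two controls are separate arms, and 3.5.2 notes that there is no published evidence on the card's effectiveness. That is a fair reason to keep the third pair, but it then belongs in 2.1, where it is absent.

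Two practical objections also stand. The analysing statistician is blinded to group coding (3.7). Tukey-Kramer runs on masked codes, whereas Dunnett must know which arm is the reference; this can be handled in the programming. And Dunnett is not the only valid two-contrast procedure. It is proposed because it gives simultaneous intervals directly.

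A reader might infer that app versus card is the smaller effect and so suffers most. The Protocol gives no expected effect per contrast, so the point does not rest on this.

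**Conclusion.** The point holds as a cheap improvement, not as an error. The primary family in 3.8.2 is larger than the question in 2.1. Matching the two would narrow both deciding intervals by 5.7% (half-width 1.25 to 1.18 points) at the same 5% familywise error and with no extra teams. It would add about 5 percentage points of power for true differences near 1 to 1.5 points. The figures assume SD 2.20, 35 analysable teams in each arm, equal variances and two-sided testing; with fewer teams the intervals widen under both procedures.

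Two stronger readings are tempting and are not supported. One is that the trial is underpowered or its primary conclusion unsafe: power at 3.00 points exceeds 99% under either procedure, and Tukey-Kramer errs on the conservative side. The other is that the sample size is wrong or should be cut: 29 is reproducible under a Tukey-based criterion, and the lower Dunnett figure rests on an inferred definition of power.

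**What to change.** Before unblinding:

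- In 3.8.2 and the abstract, define the confirmatory family for c-DEV15plus as app versus card and app versus no aid. Test both with two-sided Dunnett and report simultaneous 95% intervals.
- Report card versus no aid as a secondary contrast with an ordinary 95% interval.
- Keep 35 per arm. State in 3.8.1 that the 29 per arm was derived under Tukey-Kramer and is therefore conservative for the Dunnett analysis.
- To preserve the analyst's blinding, pre-program Dunnett with each masked arm in turn as reference, and take the app-referenced result when the codes are opened.

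The alternative, if the sponsor wants card versus no aid as a confirmatory result, is to add it to 2.1 and keep Tukey-Kramer.

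The cost is wording and a small programming change. The downsides are that card versus no aid loses familywise control and that the masked analysis needs three runs instead of one.
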